### Criteria for discontinuing or modifying allocated intervention/comparator {15b}

According to the human research ethics approval, participants may withdraw from the study at any time. Participants are informed that the Principal Investigator may terminate the study and their participation at any time if they are deemed unsuitable for participation. Such termination will not affect their usual care received. A “stopping rule” will be applied to participants who underwent knee surgery or experienced severe knee pain during the study period [40]. For any emergencies during the study, participants were encouraged to go to the Accident and Emergency department for timely care. A&E visits are documented as adverse events of the study.

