### Eligibility criteria for participants {14a}

Participants will be enrolled from eight general outpatient clinics in the New Territories East region of Hong Kong. The eligibility criteria will be screened by trained research assistants and confirmed by primary care physicians. The inclusion criteria are adults aged ≥ 45 years; a diagnosis of KOA based on the clinical criteria of the American Rheumatology College [21]; moderate-to-severe knee pain for at least 3 months, defined as a score of ≥ 4 (on a 0–10 numerical rating scale) in response to the question “What is the average level of your left/right knee pain in the past 3 months?”. Exclusion criteria include those with potentially serious knee pathology (such as inflammatory arthritis, acute trauma, or malignancy), previous knee replacement, scheduled knee joint replacement surgery within one year, and those who are unable to reliably participate, e.g., those who do not speak Chinese or unable to attend the study intervention (Table 1).

**Table 1 Tab1:** Characteristics of the people who are needed for the trial

Characteristic	The people we would expect to see included
Age	Participants need to be of age 45 or above
Sex	This study recruits both male and female participants
Gender	This study recruits both men and women participants
Race, ethnicity and ancestry	No specific race, ethnicity, or ancestry requirements were set for the recruitment of this study. However, it was required that the participants could effectively communicate in Chinese (including written and spoken Chinese)
Socioeconomic status	No specific socioeconomic status requirements were set for the recruitment of this study. However, it was required that the participants could effectively communicate in Chinese (including written and spoken Chinese)
Geographic location	Since the study was conducted in a university-affiliated primary care clinic located in Shatin, Hong Kong, the participants recruited were required to be Knee OA patients in the same primary care cluster
Other characteristics relevant to the trial	*N/A*

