### Who will be included in each analysis {27b}

All randomized participants (i.e., intervention and control group participants) will be included in the analysis.

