### How missing data will be handled in the analysis {27c}

If missing data is present, we will use linear mixed models, which is the approach to use for intention-to-treat analysis in longitudinal clinical trials with missing values [55]. Imputation of missing values before the mixed model analyses is not recommended [56].

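### The stopping rule for severe knee pain or knee surgery does not say what stops; if it ends follow-up, loss of 52-week WOMAC pain would depend on pain

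*Protocol article*

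**What the plan says.** All references are to the protocol article.

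- **Section 15b** (discontinuing or modifying the allocated intervention or comparator): a stopping rule "will be applied to participants who underwent knee surgery or experienced severe knee pain during the study period". The section gives no threshold, instrument, time window or consequence. Just before this, it says participants may withdraw, and that "the Principal Investigator may terminate the study and their participation at any time if they are deemed unsuitable for participation".
- **Section 14a** (eligibility): entry requires "moderate-to-severe knee pain for at least 3 months", defined as an average of 4 or more on a 0–10 scale, with no upper limit. People with "scheduled knee joint replacement surgery within one year" are excluded, so knee surgery in the trial would normally be an unplanned post-randomisation event.
- **Section 16** (outcomes): the primary outcome is WOMAC pain at 52 weeks.
- **Section 18** (participant timeline): both groups complete assessments at weeks 16, 32 and 52, with no exception for stopped participants.
- **Section 27b** (analysis set): "All randomized participants (i.e., intervention and control group participants) will be included in the analysis".
- **Section 27c** (missing data): "If missing data is present, we will use linear mixed models", without imputation.

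**The concern.** A rule triggered by severe knee pain acts on the construct that the trial measures. If it ends follow-up, the participants whose 52-week scores go missing are mainly those in most pain.

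The loss would probably be unequal. If RAMP works, fewer RAMP participants reach severe pain, the control arm loses more bad scores, and the estimated effect shrinks. If exercise provokes flares, RAMP could lose its bad scores and look better than it is. In an open-label trial an undefined trigger may also be applied differently by arm: RAMP participants have extra nurse sessions at which severe pain can come to light.

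The overlap with eligibility adds to this. Because the trial recruits people with moderate-to-severe pain, the rule as worded could apply to some of them from the start.

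**Working it through.** **1. The plan's own figure.** Inputs from section 19: standardised difference 0.469, power 90%, alpha 0.05 (taken as two-sided), dropout 15%.

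- Normal approximation: n = 2(1.960 + 1.282)² / 0.469² = 95.5, so 96 per arm.
- Two-sample t-test: 96.5, so 97 per arm, with power 90.1%. This matches the plan.
- Dropout: 97 / 0.85 = 114.1, about 114 per arm and 228 in total. The plan therefore allows for 114 − 97 = 17 losses per arm.

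The sample size reproduces, and the point does not depend on it.

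**2. What does the rule stop?**

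- *Only the intervention.* The section's heading supports this. Follow-up continues, sections 18 and 27b stand, and no data are lost.
- *Participation.* The neighbouring sentences on withdrawal and termination support this. So does the application to participants in general: controls receive usual care with nothing added, and section 15b says termination leaves usual care unaffected. For a control, the rule either has no practical effect, changes the comparator in an unstated way, or ends participation.

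The text does not decide between these.

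**3. Does the mixed model cover the loss?** It relies on data being missing at random given the recorded scores. That is plausible if the triggering pain was recorded at a visit. It is doubtful if the severe pain fell between visits, if the visit score itself is lost, or if the trigger was surgery.

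**4. Size, by illustration only.** The documents give no threshold, frequency or correlation, so these inputs are assumptions. Outcomes are normal with SD 1, correlation between visits is 0.5–0.7, and the true week-52 effect is 0.469.

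- Rows A–C: the effect grows linearly to week 52; cut-off 1.0–1.6 SD above the control mean.
- Rows D–E: full effect from week 16; cut-off at the worst 5–20% of controls at one visit.

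| | What is lost | Analysis | Control lost | RAMP lost | Estimate (SD) | Shrinkage |
|---|---|---|---|---|---|---|
| A | Later visits; triggering score recorded | Mixed model | – | – | about 0.47 | none |
| B | Later visits; trigger is an unrecorded between-visit episode | Mixed model | – | – | 0.44–0.46 | 2–6% |
| C | The triggering visit score itself, week 52 included | Mixed model | 11–32% | 6–22% | 0.37–0.44 | 6–21% |
| D | Everyone above the cut-off at week 16 or 32 | Completer ANCOVA | 8–31% | 3–16% | 0.40–0.45 | 5–15% |
| E | Everyone above the cut-off at week 16, 32 or 52 | Completer ANCOVA | 10–39% | 4–21% | 0.32–0.43 | 9–31% |

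Shrinkage is (0.469 − estimate) / 0.469. For the low end of C, (0.469 − 0.37) / 0.469 = 21%; for the low end of E, (0.469 − 0.322) / 0.469 = 31%. Rows A–C and D–E differ in the assumed time course and cut-offs as well as in the analysis, so the gap between them is not due to the analysis alone. None of the ranges is a bound. If follow-up continues, the rule causes no such loss or bias.

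**5. Power.** If the rule costs 5, 10, 15 or 20 percentage points beyond the 15%, t-test power at 0.469 is 88.3%, 86.2%, 83.8% or 80.9%. The planned test is baseline-adjusted ANCOVA, which does better. With correlation 0.6 the residual SD is √(1 − 0.36) = 0.8, the effect becomes 0.469 / 0.8 = 0.586, and about 83 per arm still gives roughly 96%. Bias is the issue, not power.

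**The case against.** A reader might infer that the rule removes participants on the value of the primary outcome and so contradicts the all-randomised analysis. The documents do not support that:

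- The section governs the allocated intervention or comparator. It never says that follow-up ends, WOMAC collection stops or data are excluded.
- Sections 16, 18 and 27b schedule and analyse everyone, and section 15b states no exception. Stopping an intervention while follow-up continues fits all of them.
- The trigger is severe knee pain at any time, or surgery. It is not the 52-week WOMAC score, and surgery is an intercurrent event rather than an outcome value.
- Eligibility uses average pain over the past three months, while the rule concerns pain during the study. Severe could mean a flare or a worsening, and the source cited for the rule is not at hand. It is therefore not shown that anyone meets the rule on entry.
- The illustrated bias rests on chosen inputs.

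All of this stands, and it makes the point conditional. It does not remove it: the article states the rule, places it beside sentences on ending participation, applies it to both arms and leaves its consequence open. Detailed handling of intercurrent events may well be left to the analysis plan. Whether the primary outcome is still collected after a stop is a matter of trial conduct, and analysis cannot recover it later.

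**Conclusion.** The concern holds in conditional form. Section 15b contains a rule triggered by the primary-outcome construct, undefined and open as to what it stops, in a trial that recruits people with moderate-to-severe pain. If it ends follow-up, it conflicts with sections 18 and 27b and makes loss of 52-week scores depend on pain, probably unequally by arm. If it stops only the intervention, one sentence settles the matter.

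The size is unknown. Under the assumed inputs, shrinkage of a 0.469 SD effect runs from nothing (triggering score recorded, mixed model used) to about 20% (mixed model, visit score lost), and a completer analysis can shrink it more. Every simulated bias is towards no effect. Bias in RAMP's favour through exercise-related flares is possible but was not simulated.

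This should be fixed; confidence is moderate.

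**What to change.** 1. Reconcile sections 14a, 15b, 18 and 27b. The clinical team settles what severe means, how that fits people who enter with severe pain, and what is stopped in each arm. No clinical threshold or rule is proposed here.
2. Whatever clinical rule is kept, state that the remaining scheduled WOMAC assessments, above all week 52, are collected and analysed for every randomised participant unless consent to follow-up is withdrawn.
3. Invite participants already stopped to the 52-week assessment where still possible. Recruitment closed on 12 May 2025 and the last visit is expected on 12 May 2026, so the window is limited.
4. Report stops under the rule and knee surgery by arm.
5. If stopped participants lack 52-week data, add one missing-not-at-random sensitivity analysis, for example a shift applied to their unobserved scores.

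**Cost:** a short clarification and a few extra contacts. The visits are already planned, and the HKD 100 coupon per completed assessment is already part of the retention plan.

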### Strategies to improve adherence to intervention/comparator {15c}

Participants are reminded to attend the scheduled study visits via text messages and phone calls. For participants in the intervention group, booklets were provided to record daily exercise and dietary intake as needed.

### Concomitant care permitted or prohibited during the trial {15d}

Since both intervention and control groups will continue usual care throughout the study period, referral to physiotherapy and the prescription of analgesics will be allowed. Electronic medical records should be able to retrieve the information. Other treatments such as acupuncture, herbal medicines, and over-the-counter drugs will be discouraged but allowed. Tracking of co-interventions will be done by self-reported diary and the electronic medical record. All participants will be asked to avoid intra-articular knee injection therapies during the study period. The use of co-interventions will be controlled as confounders in our analysis.

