The RN will provide updates to the PCPs on the progress of their referred patients via electronic reminders in the Clinical Management System (CMS) after each assessment session—or upon request by the PCPs. The reports will detail any strategies and actions agreed with the patients, and their progress to date. The RN will refer the patients back if they require a medication review, e.g., if patients develop side-effects after the use of pain-killers, or if they have any other medical condition that affects participation in the trial or an escalation of care. If the situation is urgent, the RN will discuss with PA on arranging an urgent medical consultation. On the other hand, if the situation is routine, the nurse will make correspondence to the electronic message on the CMS and advise the patient to report this to their PCPs during their usual clinic appointments.

Physiotherapist and dietitian will offer structured training to our RN on weight management. They will also provide on-going support and guidance on the design of individuals’ weight management plan.

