### Outcomes {16}

Demographic data such as age, gender, BMI, and duration of knee pain will be collected. The number and type of co-morbid illnesses will be recorded.

All outcome measures will be assessed at baseline, 16, 32, and 52 weeks. The primary outcome will be the Western Ontario and McMaster Universities Osteoarthritis Index (WOMAC; 5-point Likert) pain at 52 weeks. WOMAC is well-known to be the “gold standard” self-reported measure in KOA trials [19, 41]; a validated Chinese version of the WOMAC, with good internal consistency (Cronbach’s alpha > 0.7) and test–retest reliability (intraclass correlation coefficients > 0.80), will be used in this study [42].

Secondary outcomes include a set of biopsychosocial parameters: Physical function will be measured subjectively by WOMAC function subscale [42] and objectively by the 30-second chair and stand performance test [42, 43]. Lower limbs muscle mass will be measured by bioimpedance analysis [44]. Physical activity level will be measured by the Chinese International Physical Activity Questionnaire (Short form) [45]. Self-management efficacy will be measured by Pain-Self Efficacy questionnaire [46]. Generalized Anxiety Disorder-7 (GAD-7) and Patient Health Questionnaire-9 (PHQ-9) will be used to measure anxiety and depression, respectively [47, 48]. Insomnia will be measured by the 7-item Insomnia Severity Ind ex (ISI) [49], and loneliness will be measured by the 6-item De Jong Gierveld Loneliness Scale [50, 51]. EuroQuol-5D-5L (EQ-5D-5L) questionnaire will be used to measure health-related quality of life [51].

Other outcomes, including analgesics prescriptions, can be accurately recorded in the electronic medical records, but their consumption, along with over-the-counter drugs, will be logged using medication logs. To maintain a comprehensive record, patients will be provided with medication diaries to note down details such as the name, dosage, frequency, and any specific instructions for each analgesic they take. During regular assessment timepoints, patients will be asked to complete questionnaires that utilize the Timeline Followback method to inquire about their medication usage in the past 14 days. This method involves presenting patients with a calendar and having them retrospectively recall their intake of analgesics over a 14-day period [20].

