### How will be blinding be achieved {24b}

In this open-label study, blinding of physicians, nurses, and participants will not be possible. However, all data collection will be performed by trained research assistants blinded to the allocation status of the patients, and the statistician will analyse data without referring to allocation information, thus ensuring blinding.

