## Statistical methods

### Statistical methods for primary and secondary outcomes {27a}

Baseline characteristics of the two groups will be compared using the independent samples *t*-test or Mann-Whitney test for continuous variables and chi-square test for categorical variables. Tests of intervention effects on both primary and secondary outcomes at different points will be conducted using Analysis of Covariance (ANCOVA), adjusting for baseline values. All analyses will be conducted using the R statistical program [52].

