### Methods for additional analyses (e.g., subgroup analyses) {27d}

Secondary analyses include adjustments for potential confounders, such as the use of cointerventions, and exploration of the interaction effect of treatment and the potential moderators. These will all be conducted using the R statistical program.

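### Co-interventions used after randomisation are to be controlled as confounders, with no limit stated in one section; the adjusted estimate is not the effect of adding RAMP-Knee OA to usual care

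*Protocol article*

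**What the plan says.** Three sections of the protocol article bear on this.

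- Concomitant care {15d}: "referral to physiotherapy and the prescription of analgesics will be allowed" in both arms. Acupuncture, herbal remedies and non-prescription drugs are discouraged but not barred. "Tracking of co-interventions will be done by self-reported diary and the electronic medical record". The section then states: "The use of co-interventions will be controlled as confounders in our analysis". It does not say which analysis is meant.
- Statistical methods for primary and secondary outcomes {27a}: tests of the intervention effect "will be conducted using Analysis of Covariance (ANCOVA), adjusting for baseline values". No other covariate is named.
- Additional analyses {27d}: "Secondary analyses include adjustments for potential confounders, such as the use of cointerventions". The abstract likewise lists confounder adjustment under secondary analyses.

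**The concern.** The co-interventions are tracked during follow-up, so they arise after allocation. Under 1:1 randomisation such variables cannot be common causes of allocation and outcome, which is what a confounder of the treatment comparison would have to be. They can be mediators, markers of the outcome, or colliders.

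The document itself supplies routes from allocation and from pain to their use:

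- From allocation: in the RAMP arm "The RN will refer the patients back if they require a medication review". In addition, "blinding of physicians, nurses, and participants will not be possible", so those who prescribe, refer or seek other treatment know the arm. (The trial design section says double-blinded, but the blinding section describes an open-label trial.)
- From pain: the control-group section has analgesics and physiotherapy given according to need, at the physician's discretion, so users and non-users within an arm will tend to differ in symptoms.
- Analgesic use is also an outcome in its own right: "Other outcomes, including analgesics prescriptions, can be accurately recorded in the electronic medical records". The adjustment would condition one outcome on another.
- These treatments belong to the comparator. The section on the choice of comparator counts standard and private treatments as usual care.

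Holding co-intervention use fixed therefore answers a different question from the stated aim. It also opens a non-randomised comparison of users with non-users. A second problem is that {15d}, taken alone, would let an analyst put these terms into the primary model, whereas {27a} would not. The two readings give different estimates.

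**Working it through.** **1. The plan's own figure.** The sample size section gives a standardised difference of 0.469, alpha 0.05, 90% power and 97 per arm for a two-sample t-test. The exact two-sided noncentral t gives power 0.8985 at 96 per arm and 0.9015 at 97, so 97 is reproduced. It matters here only as the scale (0.469 SD) against which a bias can be judged.

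**2. Formula.** For a linear model,

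adjusted effect = total effect − Δ × β,

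where Δ is the difference in co-intervention use (RAMP minus usual care) and β is the within-arm association of use with 52-week pain, given baseline. The bias is zero if Δ = 0 or β = 0. Its sign depends on both, and the documents give neither.

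**3. By hand, on assumed inputs.**

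- Users 0.5 SD worse because pain drives use (β = +0.5), and RAMP lowers use by 20 points (Δ = −0.20): −0.469 − (−0.20 × 0.5) = −0.369 SD. The effect is understated by 0.10 SD, and 0.10/0.469 = 21%.
- Use relieves pain (β = −0.3), and RAMP lowers use from 50% to 19% (Δ = −0.31): −0.469 − (−0.31 × −0.3) = −0.562 SD. The effect is overstated.
- For |Δ| of 0.10 to 0.30 and |β| of 0.3 to 0.8, the bias is 0.03 to 0.24 SD, or 6% to 51% of 0.469. The upper end needs a large net association in one direction.

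**4. Simulation, on assumed inputs.** There were 2,000,000 patients per scenario, a total effect fixed at −0.469 SD, a baseline coefficient of 0.5 and 50% use under usual care. The co-intervention effect on pain was 0 or −0.3 SD. An unmeasured pain flare was either absent or drove both use (log-odds 1.0) and pain (0.5 SD). Negative values mean less pain under RAMP. Bias was computed before rounding.

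| Assumed mechanism | Use, usual care / RAMP | Baseline only | Plus co-intervention | Bias |
|---|---|---|---|---|
| Use relieves pain | 50% / 19% | −0.467 | −0.561 | −0.095 |
| Use relieves pain | 50% / 81% | −0.468 | −0.374 | +0.094 |
| Flare drives use and pain | 50% / 23% | −0.470 | −0.355 | +0.116 |
| Flare drives use and pain | 50% / 78% | −0.471 | −0.587 | −0.116 |
| Both together | 50% / 22% | −0.471 | −0.438 | +0.033 |
| Both together | 50% / 78% | −0.469 | −0.502 | −0.033 |
| Any, RAMP does not change use | 50% / 50% | −0.469 to −0.471 | the same | 0.000 |

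Smaller shifts in use (to 34% or 66%) with both mechanisms gave a bias of about 0.02 SD. ANCOVA on baseline alone returned −0.467 to −0.471 SD in every scenario. The adjusted estimate ran from 75% to 125% of the true effect.

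**5. Which analysis is touched.** {27a} is the section that defines the main tests, and it names baseline values only. {27d} and the abstract place confounder adjustment in secondary analyses. The sentence in {15d} names no model. Taken together, these put the co-intervention terms outside the primary model, although {15d} does not say so.

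**The case against.** The strongest reply is that the primary estimate is already protected: the dedicated statistical section keeps the main ANCOVA to baseline values, and the adjustment is declared secondary. This stands. A reader of {15d} alone might infer that the headline RAMP effect will be biased, but the document as a whole does not support that.

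A reader might also infer a loss of power. Putting 0.355 SD into the t-test formula at 97 per arm gives 0.69 instead of 0.90, and 0.369 SD gives about 0.72. Neither figure describes the planned test. The 90% belongs to an unadjusted two-sample comparison, the protocol claims no power for the co-intervention-adjusted analysis, and the formula ignores the change in residual variance when covariates are added.

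Three further points stand. The size of the bias rests on inputs the documents do not give, and opposing mechanisms can largely cancel. Nurse referral for medication review is a plausible route from allocation to use, but its direction and frequency are not stated. And nothing in the document says that the adjusted result would be presented as the better one.

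What the reply does not remove is the mislabelling. Even as a secondary analysis, adjustment for treatment taken during follow-up is not confounder control, and the article names no estimand for it. Nor does it remove the unqualified wording of {15d}.

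**Conclusion.** The point holds within limits. The document wrongly classes post-randomisation co-intervention use as a confounder, and {15d} states the adjustment without the limit that {27a} and {27d} imply. An estimate adjusted in this way does not target RAMP-Knee OA plus usual care against usual care. It may be biased in either direction: up to about 0.12 SD in the simulated scenarios, about 0.02 to 0.03 SD where both mechanisms act, and zero if RAMP does not change use. All of these rest on assumed rates and associations, so they show what is possible and do not predict the size.

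The primary 52-week WOMAC pain estimate is probably unaffected, the planned 90% power is not shown to be reduced, and no error was found in the figure of 97 per arm. The correction is worth making because the two readings lead to different models, and the choice should not remain open once outcome data by arm are available.

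**What to change.** 1. In {15d}, replace the sentence on control of co-interventions. State that the primary and main secondary analyses (the ANCOVA, or the mixed model used when data are missing) are not adjusted for co-interventions used after randomisation, and count outcomes regardless of their use.
2. In {27d}, limit confounder or covariate adjustment to variables measured before randomisation. Baseline analgesic use is an example; the assessment schedule in the outcomes section implies that it is recorded.
3. Report co-intervention use by arm. Analgesic use is already listed as an outcome; extend the reporting to the other tracked treatments.
4. If an analysis net of co-interventions is kept, drop the word confounders, label it exploratory, and define its estimand (mediation or hypothetical) and the assumptions it needs.

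The cost is a few sentences in the protocol or the analysis plan. No new data are needed, and the sample size does not change. The wording should be settled before the 52-week data are compared by arm; the last visit is expected on 12 May 2026.
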